## 9.2 SAMPLE SIZE DETERMINATION

Power and sample size calculations were based on clinically meaningful differences between treatment groups with respect to changes in the outcomes across time (i.e. intervention effect). For the primary outcome - any SV/ARA perpetration at Time 3, the detectable difference between arms was calculated based on traditional methods that assumed a fixed number of clusters as well as fixed number of subjects per cluster. Twenty-one clusters were randomized, assuming a within-cluster intra-class correlation (ICC) of 0.01 (within-school correlations for abuse perpetration, similar to our team's prior work with a related sexual violence prevention program with male athletes), and a 20% baseline SV perpetration rate in the control arm. With 866 participants (approximately 41 boys at each site) and an 80% retention rate at Time 3, we expect to have 80% power to detect an 8.3 point decrease in SV perpetration (42% relative decrease) due to the intervention. We anticipate having ample power to detect clinically meaningful changes in bystander behaviors and the secondary outcomes as well. Based on previous studies, the within-cluster ICCs for each of our secondary outcomes ranged from 0.006 to 0.01. If we assume the upper end of that range, we will have at least 80% power to detect standardized mean differences as small as 0.23 between study arms.

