## 4 STUDY DESIGN

### 4.1 OVERALL DESIGN

This study design involves a two-arm cluster-randomized-controlled trial conducted with adolescent males ages 13-19 recruited from youth-serving community agencies in Pittsburgh, PA. Twenty-one clusters from 20 neighborhoods were randomly allocated to the intervention or control arm. Participants (n=866) complete surveys prior to program implementation (baseline) and immediately following the program (end of program, EOP). Follow-up surveys are collected 3 months (T2) and 9 months (T3) after end of program. Baseline surveys are completed in-person using tablets to complete the survey online; EOP, T2, and T3 are also completed in-person on a tablet or remotely using survey links that are texted or emailed to participants using contact information provided with recruitment. Retention is facilitated by collecting detailed contact information and offering incentives for survey completion.

Randomization was performed at the neighborhood level (i.e., cluster) to reduce risk for contamination. The initial randomization included 10 clusters that were assigned to experimental or control conditions. The study statistician performed this randomization, stratifying by lead site in that neighborhood (YMCA, Urban League, or Other), such that within each stratum, each site/neighborhood had a 50/50 chance of being assigned to intervention or control. Due to a combination of lower-than-expected recruitment by neighborhood (target=96 participants each) and the interest from other community partners, we individually randomized an additional 11 neighborhoods, stratified by type of site. This resulted in a total of 21 clusters randomized, with 11 assigned to experimental and 10 assigned to control. All neighborhoods in the study met the original criteria of being socially or economically disadvantaged and/or predominantly African American.

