### 5.5 STRATEGIES FOR RECRUITMENT AND RETENTION

*Study setting*

This study involves 20 neighborhoods and 21 clusters in the Pittsburgh area; within each neighborhood, one to four different community partner organizations (referred to as “community

partners” here) participated. Neighborhoods were recruited by identifying a potential community partner who could host the program and were willing to be randomized to receive the intervention or control programming. These community partners included youth-serving organizations, YMCA, Urban League, faith-based organizations, and libraries. Additionally, we partnered with the county’s community intensive surveillance program, a diversion program for youth involved in the juvenile justice system.

Neighborhoods were identified based on having sites where the YMCA, Urban League, or other youth serving partners had existing programs and which were considered lower income communities based on census information and school district data. Asset maps were created for each neighborhood with the goal of identifying community champions and youth-relevant resources to support this community-based project. The strong partnerships established with key stakeholders in each of these sites (including site coordinators, facilitators, and community members) facilitated recruitment and retention as described below.

Among the 20 participating neighborhoods, the proportion of students attending public high schools in those neighborhoods considered economically disadvantaged ranges from 32-100%; the high school graduation rate for those same school districts ranged from 63-97%. Each of these neighborhoods struggle with poverty, school ‘push-out’ (disciplinary actions that push youth, especially African American boys, out of the regular school system), and among the highest rates of gang and gun violence in the county (see Table 2 for neighborhood characteristics). These characteristics were compared by treatment arm using Kolmogorov-Smirnov two-sample exact tests due to their non-normal distributions. Neighborhood characteristics did not vary between the intervention and control arm neighborhoods.

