Within the 20 participating neighborhoods, there were a total of 40 sites/community partners/locations approached and 38 agreed to participate. The composition of the participating sites included 11 places of worship, 20 community centers, 2 public libraries, and 5 juvenile justice community intensive surveillance program centers. One site (cluster) was located at the downtown Urban League office and consisted of youth involved in an African American young men’s leadership group who came from several different neighborhoods and schools in the Pittsburgh area.

For recruitment of eligible youth, we rely on this network of community partners identified in asset maps created for each neighborhood cluster. This includes site leaders, program facilitators, recruiters with strong connections to their community, prevention specialists embedded in schools, school districts that offer community-based programs as an alternative to suspension, and the Community Intensive Supervision Program (CISP) for youth involved in the juvenile justice system.

Using respondent driven sampling (RDS), former and current participants may refer their friends to the program. Participants interested in RDS receive a packet of information on how to recruit a friend or neighbor and five recruitment coupons. When newly-recruited participants come to their first session and turn in their recruitment coupon, the peer recruiter is compensated \$5, up to \$25 overall.

Once community partners recruit youth, retention throughout the 18-hour curriculum is a key focus. Upon enrolling in either the control or experimental arm, prospective participants receive program information, sign an assent form and complete a contact information sheet. Research assistants ensure that the document is legible and that all fields are completed. Research assistants use this information to contact the participant prior to each session to remind them of the session. If youth are not present at the beginning of a session, research assistants and facilitators will contact the participant to encourage them to join late.

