### 6.3 MEASURES TO MINIMIZE BIAS: RANDOMIZATION AND BLINDING

#### Assignment of Interventions

##### Randomization

Randomization was performed at the neighborhood level (i.e., cluster) to reduce risk for contamination. The initial randomization included 10 clusters that were assigned to experimental or control conditions. The study statistician performed this randomization, stratifying by lead site in that neighborhood (YMCA, Urban League, or Other), such that within each stratum, each site/neighborhood had a 50/50 chance of being assigned to intervention or control. Due to a combination of lower-than-expected recruitment by neighborhood (target=96 participants each) and the interest from other community partners, we individually randomized an additional 11 neighborhoods, stratified by type of site. This resulted in a total of 21 clusters randomized, with 11 assigned to experimental and 10 assigned to control. All neighborhoods in the study met the original criteria of being socially or economically disadvantaged and/or predominantly African American.

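### Power and detectable differences assume equal cluster sizes, which the described recruitment makes implausible, so the stated figures are probably somewhat too favourable

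*Protocol*

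**What the plan says.** Protocol section 9.2 (repeated in 4.3) states that the detectable difference for the primary outcome used "traditional methods that assumed a fixed number of clusters as well as fixed number of subjects per cluster". Its inputs are: "Twenty-one clusters were randomized, assuming a within-cluster intra-class correlation (ICC) of 0.01"; "a 20% baseline SV perpetration rate in the control arm"; and "With 866 participants (approximately 41 boys at each site) and an 80% retention rate at Time 3". Since 866/21 = 41.2, the word site in that last phrase must mean the randomized cluster. From these the protocol claims 80% power for an 8.3-point decrease and, at the same ICC for the secondary outcomes, 80% power for an SMD of 0.23. Neither figure carries an allowance for clusters of different size.

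Other sections describe how the clusters filled. Section 4.1 explains the addition of 11 clusters to the first 10: "Due to a combination of lower-than-expected recruitment by neighborhood (target=96 participants each"). Section 5.5 says that "within each neighborhood, one to four different community partner organizations" took part, and that "there were a total of 40 sites/community partners/locations approached and 38 agreed to participate". Those 38 sites were places of worship, community centers, libraries and juvenile justice program centers. One cluster was a downtown leadership group drawing youth from several neighborhoods. Section 6.3 gives the allocation: a "total of 21 clusters randomized, with 11 assigned to experimental and 10 assigned to control".

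**The concern.** A calculation with one common cluster size gives the right design effect only if the clusters really are about equal. Here some clusters were opened with a target of 96 and others were added later. The number of hosting organizations varied from one to four, and the host types differed widely. Enrolment near 41 in every cluster would be surprising.

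The direction of the error is known: at a given mean size and ICC, unequal sizes increase the design effect, so ignoring them flatters the power. What is at stake is how a null primary result is read. It would be set against a sensitivity of 80% for 8.3 points that the design may not have, and the 0.23 SMD for the secondary outcomes is exposed in the same way. Because 866 is given as the trial's number of participants, the 21 sizes should be available to the sponsor, and an equal-size assumption is not needed.

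**Working it through.** **Inputs.** From section 9.2: 21 clusters, 866 youth, ICC 0.01, 20% in control against 20 − 8.3 = 11.7% under intervention, 80% retention. From 6.3: 10 control and 11 intervention clusters. From 9.4.1: two-sided 5%. Assumed: the CV of cluster size (SD divided by mean), which the protocol does not give.

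**Formulas.** Let m be the mean cluster size.
- Equal sizes: DEFF = 1 + (m − 1) × ICC.
- Unequal sizes, conservative form: DEFF = 1 + ((1 + CV²) × m − 1) × ICC.
- Unequal sizes, milder form suited to a mixed model: the equal-size DEFF divided by (1 − CV² × L × (1 − L)), where L = m × ICC / (m × ICC + 1 − ICC).
- SE = √[DEFF × (0.2 × 0.8/n_C + 0.117 × 0.883/n_I)].
- Power = Φ(0.083/SE − 1.96).
- Detectable SMD = 2.80 × √[DEFF × (1/n_C + 1/n_I)].

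**Step 1: reproduce the plan's figures.** With all 866 youth, m = 41.24, n_C = 866 × 10/21 = 412.4 and n_I = 866 × 11/21 = 453.6. DEFF = 1 + 40.24 × 0.01 = 1.402. SE = √[1.402 × (0.000388 + 0.000228)] = 0.0294. Power = Φ(2.825 − 1.96) = 80.6%. The detectable difference is 8.24 points and the SMD 0.226. (A pooled variance gives 80.8% and 8.22 points.) So the plan's figures correspond to equal clusters with no dropout.

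**Step 2: choose CVs to illustrate.** One proxy is size proportional to the number of sites, with 38 sites over 21 clusters (mean 1.81), one to four each and both extremes present. The most even split is 6 clusters with one site, 14 with two and 1 with four: CV = √(78/21 − 1.81²)/1.81 = 0.37. The least even is 15 with one, 1 with three and 5 with four: CV = √(104/21 − 1.81²)/1.81 = 0.72.

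**Step 3: all 866 analysed, unequal clusters.** Ranges run from the milder to the conservative form.

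| CV | DEFF | Power | Detectable points | SMD |
|---|---|---|---|---|
| 0 | 1.402 | 80.6% | 8.24 | 0.226 |
| 0.37 | 1.443–1.459 | 79.5–79.1% | 8.35–8.39 | 0.229–0.230 |
| 0.50 | 1.479–1.505 | 78.5–77.8% | 8.44–8.51 | 0.232–0.234 |
| 0.72 | 1.571–1.616 | 76.1–74.9% | 8.67–8.78 | 0.239–0.242 |

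Power passes below 80% at a CV of about 0.25 to 0.3, depending on the form and on the variance used.

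**Step 4: the stated 80% retention.** Now N = 0.8 × 866 = 692.8, m = 33.0 and the equal-size DEFF is 1.320. Equal clusters give 74.0% power, 8.86 points and SMD 0.245. At CV 0.37 power is 72.9 to 72.6%; at CV 0.72 it is 69.6 to 68.8%. Unequal sizes therefore take roughly another 1 to 5 points.

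**The case against.** The protocol discloses the simplification in words, so this is a planning approximation rather than a wrong sum. No section gives a cluster size, range or CV. A reader might infer that the recruitment account rules out equal sizes and that the design cannot deliver 80% power even with nobody lost. The documents do not support that: the missed target shows low recruitment, not its spread, and below a CV of about 0.25 to 0.3 the no-dropout figures survive.

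Nor is 0.37 to 0.72 a bound from the protocol. It assumes enrolment proportional to site count, which is nowhere stated. It also carries a count of organizations per neighborhood (20 of these) over to 21 clusters. Partners could have been added where recruitment was low, which would even the sizes out. A reader might also take some clusters to be libraries or surveillance centers; section 5.5 lists these as site types within neighborhoods.

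The planned analysis (9.4.2) is a mixed model with random cluster effects, which loses less than the conservative formula implies. Adjustment for baseline perpetration could recover some precision, though no correlation is given to quantify it. At CV 0.37 the change is close to rounding. Enrolment, model and test are unaffected, and confidence intervals will show the achieved precision.

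All of this limits the size of the effect. It does not make equal clusters plausible, and it does not change the direction of the error.

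**Conclusion.** The point holds in a qualified form. The protocol fixes an equal-size assumption that its own recruitment account makes implausible, and the error can only be favourable. The stated 80%, 8.3 points and 0.23 are probably somewhat optimistic; by how much cannot be read from the protocol. On the assumed CVs of 0.37 to 0.72, the no-dropout loss runs from about 1 point of power to just under 6 (80.6% to 74.9%), and the SMD reaches at most 0.242. This rests on ICC 0.01, 20% against 11.7%, an 11:10 split, normal quantiles and no gain from baseline adjustment.

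The larger shortfall needs no assumed CV and is a separate matter: the stated figures match full enrolment, whereas the 80% retention that the text says it includes gives 74.0% with equal clusters. Unequal sizes add to that gap and are not its cause, but correcting retention alone would probably still leave a figure that is too favourable.

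**What to change.** In sections 9.2 and 4.3, replace the fixed-size assumption with the 21 actual cluster sizes, or their mean and CV. Use a design effect for unequal clusters that suits the planned mixed model, and give 1 + ((1 + CV²) × m − 1) × ICC as the conservative form. Restate the power, the detectable percentage-point difference and the detectable SMD at the retained sample size, in the same revision as the retention correction. The cost is one recalculation from data the sponsor should hold and a change of wording in two sections. The stated power will probably come out lower; no extra enrolment and no change to the analysis model is needed.

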### Primary Outcome:

**SV/ARA perpetration:** At baseline and T3 (9 months post-intervention), participants report whether they perpetrated the following SV or ARA behaviors in the last 9 months. The primary outcome measure for the study is any report of SV or ARA perpetration, i.e., yes to any of the following items.

The following two constructs focus on ARA behaviors against a dating partner. "Any ARA perpetration" is measured as a yes to any of these 13 items.

**Physical/Sexual relationship violence:** Three items are used to assess physical or sexual violence perpetration against a partner or ex-partner.(33) Participants report whether they performed each action, which is dichotomized as yes to any. Examples include "hit, pushed, slapped, choked or otherwise physically hurt someone you were going out with or hooking up with?" and "used physical force or threats to make someone you were going out with or hooking up with have sex (vaginal, oral, or anal sex) when they didn't want to?"

**Dating abuse:** A ten-item scale, developed for use with high school-aged students, is used to assess whether the participant perpetrated any abuse against a dating partner (34). Examples include "convinced them to have sex, after they said no a few times" and "told them not to talk to others or told them who they could hang out with." A positive response to any of these items is counted as any ARA perpetration.

"Any SV perpetration" is measured as yes to any of the sexual relationship violence and dating abuse items above as well as yes to any of the behaviors below.

**Non-partner sexual violence:** To measure whether a participant committed sexual violence against a *non-partner*, the two sexual IPV items were modified to query for people they had NOT gone out with or hooked up with, and included friends, family, and strangers (33). Responses are dichotomized as yes to any.

**Incapacitated sex:** Participants are asked if they had done something sexual with someone when that person was "too drunk or high to stop you,"(35) with a response of "yes" coded as yes to incapacitated sex.

**Use of drugs or alcohol on purpose for sex:** Participants are asked whether they had purposely given someone alcohol or drugs to do something sexual with that person(36). A response of "yes" is coded as yes to use of drugs or alcohol on purpose for sex.

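### Section 9.2 powers the any-SV/ARA primary outcome with a rate and an effect labelled SV, and its 8.3 points at 80% power does not follow from its own inputs once the stated retention is applied

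*Protocol*

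**What the plan says.** Protocol section 9.2 opens by tying the calculation to the primary endpoint: "For the primary outcome - any SV/ARA perpetration at Time 3, the detectable difference between arms was calculated". Its inputs are then "a 20% baseline SV perpetration rate in the control arm", "assuming a within-cluster intra-class correlation (ICC) of 0.01", "With 866 participants (approximately 41 boys at each site") and "an 80% retention rate at Time 3". Its conclusion is "80% power to detect an 8.3 point decrease in SV perpetration (42% relative decrease"). Section 4.3 prints the same text. Section 6.3 gives the allocation as "a total of 21 clusters randomized, with 11 assigned to experimental and 10 assigned to control". Section 9.4.1 sets two-sided tests at 5%.

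Section 8.1 defines the endpoint: "The primary outcome measure for the study is any report of SV or ARA perpetration, i.e., yes to any of the following items". It also defines two narrower outcomes, any ARA and any SV, each with its own item list. No rate for the composite appears anywhere in the protocol.

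**The concern.** In a binary power calculation the control rate fixes the variance, so it has to describe the outcome being tested. Here the calculation is introduced for one outcome, while its rate and its result carry the label of another that the protocol defines separately. A reader cannot tell whether 20% is the expected rate of the primary endpoint.

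The stated figure also has to follow from the stated inputs, whichever outcome the 20% describes. Sections 9.2 and 4.3 hold the only sample-size justification for the primary endpoint. If 8.3 points at 80% power is not what 866 boys with 80% retention deliver, the protocol promises more precision than the design has.

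**Working it through.** **Inputs.** 866 enrolled, 80% retention, 21 clusters, ICC 0.01, control rate 20%, decrease 8.3 points (20% to 11.7%, which is 8.3/20 = 41.5% relative), all from 9.2; 10 control and 11 experimental clusters from 6.3; two-sided 5% from 9.4.1.

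**Method.** Design effect DE = 1 + (m − 1) × ICC, with m the number analysed per cluster. Effective n per arm = clusters × m / DE. SE = √[p₁(1 − p₁)/n₁ + p₂(1 − p₂)/n₂]. Power = Φ(difference/SE − 1.960). The detectable decrease is the difference that equals (1.960 + 0.842) × SE.

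**Step 1: the protocol's figure without attrition.**
- m = 866/21 = 41.24; DE = 1 + 40.24 × 0.01 = 1.402
- n₁ = 412.4/1.402 = 294.1; n₂ = 453.6/1.402 = 323.5
- SE = √(0.2 × 0.8/294.1 + 0.117 × 0.883/323.5) = 0.02939
- Power = Φ(0.083/0.02939 − 1.960) = Φ(0.865) = 80.6%; detectable decrease 8.2 points

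This matches the stated 8.3 points at 80%.

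**Step 2: with the stated 80% retention.**
- m = 866 × 0.8/21 = 32.99; DE = 1 + 31.99 × 0.01 = 1.320
- n₁ = 329.9/1.320 = 249.9; n₂ = 362.9/1.320 = 274.9
- SE = √(0.2 × 0.8/249.9 + 0.117 × 0.883/274.9) = 0.03187
- Power = Φ(0.083/0.03187 − 1.960) = Φ(0.644) = 74.0%; detectable decrease 8.9 points (44% relative)

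**Variants with retention applied.** A pooled null variance gives 74.3% and 8.8 points; the arcsine method 74.6%; 11 v 11 clusters 76.1%; a t reference on 19 df 69.5%. ICC 0.006 gives 78.5% and a one-sided test 83.3%, but neither is an input of this calculation.

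The standardized difference of 0.23 in the same section shows the same pattern. With (1.960 + 0.842) × √(1/n₁ + 1/n₂), it is 0.226 without attrition and 0.245 with it.

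**Step 3: how far apart are SV and the composite?** Counting items in 8.1:
- Composite: 3 physical/sexual partner violence + 10 dating abuse + 2 non-partner + 1 incapacitated + 1 drugs or alcohol + 5 harassment + 3 cyber = 25
- Any SV, read literally: 2 sexual partner violence + 10 + 2 + 1 + 1 + 5 + 3 = 24

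Only the physical partner-violence item lies outside. If the word sexual is taken to restrict the dating abuse items as well, the gap is wider, but the protocol gives no size for it.

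**Step 4: sensitivity to the composite rate.** The composite contains every SV item, so its rate is at or above the SV rate measured on those same items. The rates below are assumptions, with the other inputs as in step 2.

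| Control rate | Detectable decrease, points | Relative | Power for 8.3 points | Power for 41.5% relative |
|---|---|---|---|---|
| 20% | 8.9 | 44% | 74% | 74% |
| 30% | 10.5 | 35% | 58% | 92% |
| 40% | 11.6 | 29% | 51% | 98% |
| 50% | 12.1 | 24% | 48% | >99% |

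The two ways in which 9.2 states its target coincide only at 20%. Above that they move in opposite directions.

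**The case against.** The strongest defence is that SV is shorthand. Section 9.2 has just named any SV/ARA, it justifies the ICC by abuse perpetration in general, and under the definition in 8.1 SV and the composite differ by a single item. This stands as far as it goes. A reader might infer that the 20% belongs to a much narrower outcome and that no effect is stated for the primary endpoint at all. The protocol does not support that: it says the calculation is for the primary outcome and never says where the 20% comes from. The shorthand reading still leaves the label to be corrected, because 8.1 gives SV its own meaning, and it does not repair the arithmetic, since step 2 already takes 20% as the composite rate.

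A reader might also infer from the power for 8.3 points at 40% or 50% that the trial has about even odds of success. That does not follow. Those rates are assumed, and at the same rates the stated relative decrease becomes easier to detect.

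Two limits also stand. The primary model in 9.4.2 adjusts for baseline perpetration and this calculation does not, so actual power may differ; 9.2 gives no baseline-to-follow-up correlation from which to claim a gain. And a null result would be read from the estimate and its confidence interval, so a loose planning figure does not make it uninterpretable.

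**Conclusion.** The concern holds in two limited parts. First, the outcome label in 9.2 and 4.3 is inconsistent, and the rate that the calculation needs, that of any SV/ARA, is not identified; how much this matters cannot be sized from the protocol. Second, the headline figure does not follow from its inputs. With 80% retention, power for 8.3 points is about 74% instead of 80%, and the detectable decrease is about 8.9 points (44%) instead of 8.3 (42%).

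The second part rests on the protocol's own ICC, allocation and two-sided 5% level, with equal cluster sizes, a normal reference and no covariate adjustment. The shortfall is modest, about 0.6 points. A composite rate above 20% would make 8.3 points and 42% different targets, but would not by itself show that the trial is underpowered.

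**What to change.** In 9.2 and 4.3:
- Name any SV/ARA perpetration as the outcome throughout the power text.
- Replace the 20% by the composite prevalence from the baseline survey, pooled across arms without unblinding, and use the ICC from the same data. Baseline and Time 3 use the same 9-month recall.
- Apply the 80% retention and restate the detectable decrease in both absolute and relative terms. If 20% is kept, that is about 8.9 points, or 44%.
- Recompute the 0.23 standardized difference in the same pass.

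Do not change N. The cost is one arm-blind tabulation of data already collected and a few revised sentences. At an unchanged 20% rate, the stated detectable decrease becomes slightly less favourable.

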## 9.4 STATISTICAL ANALYSES

### 9.4.1 GENERAL APPROACH

Generalized linear mixed models will be used to account for the correlation among youth from the same cluster as well as the correlation between observations from the same youth. Descriptive statistics will be used to summarize the sample with regard to baseline characteristics of interest. Means and standard deviations will be presented for continuous variables, while sample proportions will be provided for categorical variables. 95% confidence intervals will accompany all sample statistics. Primary assessment of intervention effects will be based on intent-to-treat estimates. As-treated, or treatment-on-the-treated (TOT), effect parameters will be estimated in secondary analyses and reported as exploratory. Between-site differences regarding intervention effects will be assessed based on level of staff/facilitator engagement in curricular delivery as well as other observed external factors that may interact with the intervention to alter outcomes. SAS software will be used for all statistical analyses.

To assess differences at baseline between the youth in the experimental and control groups, demographics such as grade-level, race, nativity, and parental education will be compared while accounting for within-neighborhood clustering. Demographic variables as well as neighborhood-level characteristics resulting in between-arm imbalances will be considered as covariates in the primary and secondary analyses.

Participation bias will be assessed by comparison of age and race/ethnicity of youth participating in the study compared to the overall demographics of adolescents (school district and census data). Significant differences detected via chi-square analysis will be noted as potential validity threats.

An attrition analysis will be conducted by comparing youth who completed follow-up surveys with those who did not with regard to demographics as well as outcomes measured at baseline. All hypotheses will be two-sided tests with a significance level of 5%.

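### The stated 80% power for an 8.3-point decrease does not follow from the stated inputs at 80% Time 3 retention; they give about 74%

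*Protocol*

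**What the plan says.** Protocol Section 9.2 sets out the power calculation for any SV/ARA perpetration at Time 3. The method is described only as traditional, with a fixed number of clusters and a fixed number of subjects per cluster. The inputs are:

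- twenty-one clusters, "assuming a within-cluster intra-class correlation (ICC) of 0.01";
- "a 20% baseline SV perpetration rate in the control arm";
- "With 866 participants (approximately 41 boys at each site".

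The conclusion reads: "an 80% retention rate at Time 3, we expect to have 80% power to detect an 8.3 point decrease in SV perpetration", glossed as a 42% relative decrease. For the secondary outcomes, taking the upper end of an ICC range of 0.006 to 0.01, it says "we will have at least 80% power to detect standardized mean differences as small as 0.23 between study arms". Section 4.3 repeats this paragraph.

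Section 6.3 gives the allocation as 11 experimental and 10 control clusters. Section 9.4.1 says "All hypotheses will be two-sided tests with a significance level of 5" per cent.

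**The concern.** The sentence names 80% retention as one of the conditions under which 8.3 points is detectable, so a reader will take it that attrition is already allowed for. The figure is close to what all 866 enrolled youth would give, and not to what about 693 would give. If so, the type II error implied by the stated inputs is about 26% rather than 20%. This paragraph is also what a reader would use to judge whether a null primary result speaks against a 42% relative reduction.

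**Working it through.** **Inputs.** 866 enrolled, 21 clusters, ICC 0.01, 20% control rate and 80% retention (Section 9.2); 10 control and 11 experimental clusters (Section 6.3); two-sided 5% (Section 9.4.1). The 20% is taken as the control rate at Time 3, which is what the 42% gloss implies (8.3/20 = 41.5%). The intervention rate is then 11.7%.

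**Formulas.** With *m* analysed per cluster and *k* clusters in an arm:

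- design effect DE = 1 + (*m* − 1) × 0.01
- effective sample size per arm *n* = *k* × *m* / DE
- SE = √(0.20 × 0.80 / *n*₁ + 0.117 × 0.883 / *n*₂)
- power = Φ(0.083 / SE − 1.960)

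This uses unpooled variance. The pooled version was also run.

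**Step 1: the plan's figure, no attrition.** *m* = 866/21 = 41.24 and DE = 1 + 40.24 × 0.01 = 1.402. Effective *n* = 294.1 (control) and 323.5 (experimental).

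- SE = √(0.16/294.1 + 0.1033/323.5) = 0.02939
- 0.083/0.02939 = 2.825; power = Φ(0.865) = 80.6% (pooled 80.8%)
- Difference detectable with 80% power: 8.24 points (pooled 8.22)

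Rounding *m* to 41 gives power of 80.5 to 80.7% and 8.25 points (pooled 8.24). The stated 80% and 8.3 points are therefore approximately reproduced with everyone analysed.

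**Step 2: the stated 80% retention.** Analysed = 0.8 × 866 ≈ 693, *m* = 32.99 and DE = 1 + 31.99 × 0.01 = 1.320. Effective *n* = 249.9 and 274.9.

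- SE = √(0.16/249.9 + 0.1033/274.9) = 0.03187
- 0.083/0.03187 = 2.604; power = Φ(0.644) = 74.0% (pooled 74.3%)
- Difference detectable with 80% power: 8.86 points (pooled 8.84); 8.86/20 ≈ 44% relative

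On the pooled formula, 80% power for 8.3 points needs about 97% retention.

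**Step 3: what would restore 80% at 693.**

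| Change | Power for 8.3 points | Agrees with the text? |
|---|---|---|
| One-sided test | 83% | No: tests are two-sided |
| ICC 0.006 | 78.5% | No: 0.01 is stated |
| Baseline–Time 3 correlation 0.36, variance × (1 − 0.36²) = 0.87 | about 80% | Not stated |

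**Step 4: secondary outcomes.** Detectable SMD = (1.960 + 0.842) × √(1/*n*₁ + 1/*n*₂), with the same effective sizes at ICC 0.01.

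- No attrition: 2.802 × 0.08057 = 0.226, which rounds to the stated 0.23
- 80% retention, if it applies here: 2.802 × 0.08740 = 0.245; power for 0.23 is 75%

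**Sensitivity.** Replacing the normal reference with a *t* reference on 21 − 2 = 19 df, at 80% retention, gives about 70% power for 8.3 points. The detectable difference becomes about 9.3 points and the detectable SMD about 0.26.

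**The case against.** The strongest reply is baseline adjustment. Section 9.2 says the calculations concern changes in outcomes over time, and the primary model in Section 9.4.2 includes baseline perpetration. A baseline-to-Time 3 correlation near 0.36 would bring power at 693 back to 80%. This stands in part. It does not rescue the sentence, because no correlation is given. But a reader might infer that the trial itself lacks 80% power, and the documents do not support that. They show only that the stated inputs do not produce the stated power.

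A reader might also infer that retention was simply forgotten. The agreement at about 41 per cluster suggests this, but the match is approximate and neither formula nor software is given. The cause cannot be established from the protocol.

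A third tempting reading is that true power is 70%. That rests on the 19-df reference, which the protocol neither adopts nor excludes; it is a methodological choice and not an arithmetic error.

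The SMD sentence names no retention rate, and Aim 1 tests these outcomes at about 3 months, for which none is given. The shortfall there depends on carrying the Time 3 figure across. Aim 2 does assess the same outcomes at Time 3, so that is reasonable, but it is an assumption.

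Finally, the intention-to-treat population is all enrolled youth and multiple imputation is foreseen. Imputation does not recreate the information in 866 observed outcomes, and Section 9.2 itself treats retention as an input to power.

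**Conclusion.** The point holds for the primary outcome. On the protocol's own inputs and a normal reference, 80% retention gives about 74% power for 8.3 points, or 80% power for 8.8 to 8.9 points. The discrepancy is about 6 percentage points of power, or about half a point in the detectable difference (42% to about 44% relative). It rests on equal cluster sizes, as the protocol assumes, the 11 versus 10 split, and no credit for baseline adjustment. Pooled and unpooled variances agree to within 0.3 percentage points of power.

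The SMD of about 0.245 rather than 0.23 is a secondary remark, conditional on the same retention. The 19-df values are sensitivity figures only. No endpoint or analysis is affected; the stated operating characteristic should be corrected.

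**What to change.** In both Section 9.2 and Section 4.3, do one of the following:

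- restate the difference detectable with 80% power at 80% retention as about 8.8 to 8.9 points (about 44% relative); or
- keep 8.3 points and state power as about 74%.

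If a gain from baseline adjustment is relied on, state the assumed baseline-to-Time 3 correlation (about 0.36 is needed to keep 80% at 8.3 points) and its source. For the SMD, state the retention and time point assumed; if 80% at Time 3, give about 0.245, or about 75% power for 0.23. The 19-df values could be added as a labelled sensitivity.

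The cost is wording in two sections and a slightly less favourable figure. No participants are added and neither design nor analysis changes.
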